## Abstract

**Background:**

The appropriate care for people with cardiovascular risk factors can reduce morbidity and mortality. One strategy for improving the care for these patients involves the implementation of evidence-based guidelines. To date, little research concerning the impact of such implementation strategies in our setting has been published. Aims. To evaluate the effectiveness of a multifaceted tailored intervention in the implementation of three cardiovascular risk-related guidelines (hypertension, type 2 diabetes and dyslipidemia) in primary care in the Basque Health Service compared with usual implementation.

**Methods/Design:**

A two-year cluster randomized clinical trial in primary care in two districts in the Basque Health Service. All primary care units are randomized. Data from all patients with diabetes, hypertension and those susceptible to coronary risk screening will be analyzed.

Interventions. The control group will receive standard implementation. The experimental group will receive a multifaceted tailored implementation strategy, including a specific web page and workshops for family physicians and nurses.

Endpoints. Primary endpoints: annual request for glycosylated hemoglobin, basic laboratory tests for hypertension, cardiovascular risk screening (women between 45–74 and men between 40–74 years old). Secondary endpoints: other process and clinical guideline indicators.

Analysis: Data will be extracted from centralized computerized medical records. Analysis will be performed at a primary care unit level weighted by cluster size.

**Discussion:**

The main contribution of our study is that it seeks to identify an effective strategy for cardiovascular guideline implementation in primary care in our setting.

**Trial registration:**

Current Controlled Trials, ISRCTN88876909

## Background

### Diabetes and cardiovascular risk factors

High blood pressure, dyslipidemia and diabetes are the main clinical conditions presented by patients with multiple morbidities [1].

Cardiovascular disease is the leading cause of death in both the Basque Country and Spain as a whole. Despite this, cardiovascular disease-related mortality has decreased over the past few years due, amongst other reasons, to the better diagnosis and treatment of cardiovascular risk factors [2].

Current data suggest that there remains significant room for improvement in cardiovascular risk factor and diabetes care in our setting. According to data from the Provider Agreement in 2008 only 41.3% of diabetic patients in the Autonomous Community of the Basque Country had a glycosylated hemoglobin (HbA1c) level of less than 7.5%, basic analysis was performed in 44.9% of patients and only 27% had a blood pressure of less than 140/80 mm Hg.

The almost anecdotal use of tools to calculate cardiovascular risk at that time suggests that statin treatment in primary prevention is chosen on the basis of cholesterol level rather than overall cardiovascular risk [3].

As far as hypertensive patients in our setting are concerned, it is estimated that only 33% have their blood pressure well controlled and that 46.4% do not receive the antihypertensive agent of choice [4].

### Clinical practice guidelines as a tool for improving healthcare

The implementation of evidence-based clinical practice guidelines (CPGs) may help to ensure that the care of patients with cardiovascular risk factors or diabetes complies with the best quality criteria and standards.

CPGs are statements that include recommendations intended to optimize patient care which are informed by a systematic review of evidence and an assessment of the benefits and harms of alternative care options [5]. As such, they have the potential to reduce variability and improve healthcare [6].

In the past few years we have witnessed the consolidation of a CPG program in both the Basque Country and the Spanish National Health System as a whole that has led to the Guiasalud program [7], the development of a common methodology for drafting such guidelines [8] and the availability of an increasing number of guidelines prepared in Spain.

Thus, in the cardiovascular field, 2008 and 2009 saw the publication of the “Clinical practice guideline on the management of lipids as a cardiovascular risk factor” [9], an update to the regional “Clinical practice guideline on arterial hypertension” [4] and the “Clinical practice guideline on type 2 diabetes” [10], the latter of which was drafted within the framework of the National Health System's Clinical Practice Guideline Program in collaboration with the Health Technology Assessment Agency Osteba. These three guidelines are available from Guiasalud [7] and have been included in the National Guideline Clearinghouse.

### Design of CPG implementation strategies

The publication and dissemination of a CPG does not, however, ensure its application in clinical practice, therefore effective and viable implementation plans for the organizational context at which it is aimed must be designed. Implementation must be considered to be a planned process whose main characteristics are dynamism and uniqueness [6].

It is important that guideline implementation interventions are designed in accordance with a coherent theoretical foundation, a body of evidence to support them and taking into account the barriers and facilitators of the local setting [6,11-13].

#### **
*Theoretical foundation*
**

Grol’s 10-step model [11] is a theoretical reference for guideline implementation [6]. This model brings together elements from different disciplines, such as the diffusion of innovation theory [14], the reasoned action theory [15] and social cognitive theory [16], and postulates that professionals pass through different phases or stages (orientation, insight, acceptance, change and maintenance) when achieving a change, with specific barriers predominating in each phase. This study concentrates on the orientation, insight and acceptance phases.

#### **
*Barriers and facilitators*
**

Although there are numerous studies concerning the barriers and facilitators for CPG implementation [17], this is not the case in our setting. As a result, before designing the guideline implementation intervention, we undertook a study to explore the barriers faced by CPGs in primary care using the Delphi technique [18]. The main barriers detected are the following [18].

Dimension: Presentation of the guidelines**:**

– The teaching method used by the speakers at each session.

– The choice of speaker.

Dimension: Format of the guidelines:

– The need for a summarized version.

– The need to stimulate and promote the on-line version, which makes term search easier, and the links within the guidelines and to other material of interest.

– The need to enhance user participation (discussion fora, asking questions, debates, etc.).

Dimension: Use and utility facilitators:

– Application of CPGs gives good results in clinical practice.

– The need to attach action protocols or other practical tools to the guidelines.

Internal barriers:

– Willingness of the physicians themselves.

– Too much time and effort required to understand the CPGs.

– Lack of acceptance of guidelines as a work tool.

– Discouragement due to lack of use at other healthcare levels.

External barriers:

– Specialized practice does not follow the guidelines.

– Lack of dissemination and implementation in specialized care.

– Pressure from the pharmaceutical industry.

– Methodology followed to learn the guidelines.

#### **
*Effectiveness of guideline implementation interventions*
**

According to Grimshaw’s systematic review [12], the effectiveness of different clinical practice guideline dissemination and implementation strategies varies but, in general, tends to be modest. The dissemination of educational materials tends to be poorly effective but at low-cost, whereas continual medical training is more effective if undertaken in small groups using realistic scenarios [19-21]. The efficacy of opinion leader-based training tends to vary [12]. Multifaceted interventions appear to make sense if they are intended to overcome specific barriers [19]. Indeed, tailored interventions are more effective than passive guideline dissemination [13].

In the field of diabetes, the review by Shojania [22] showed that multifaceted interventions provided a larger effect than interventions involving a single component. Educational interventions showed an acceptable efficacy. In the field of hypertension, educational interventions aimed at healthcare professionals resulted in a modest improvement in blood pressure control [23]. The most effective strategy for implementing the use of risk tables in cardiovascular disease prevention is still unknown [24].

#### **
*Context*
**

The intervention and study were designed in the context of a primary care research group with a clinical and/or methodological profile involved in the drafting and implementation of evidence-based guidelines. The intervention was aimed at primary care professionals (physicians and nurses) and no organisational changes or interventions in patients were considered. A further assumption was that the proposed interventions had to be feasible and result in a reasonable cost to the health system.

As no single implementation strategy is effective in all contexts, the impact of such strategies needs to be evaluated by way of studies with a robust design and low risk of bias. Randomized designs are the gold-standard for assessing healthcare interventions [12,25].

Although we are witnessing significant support for the drafting of CPGs by public health organisations in Spain, evaluation of their subsequent implementation remains uncommon [26].

In our setting, the availability of three recently published CPGs in the cardiovascular field provides a unique opportunity to assess CPG implementation strategies in primary care.

### Main endpoint

To evaluate the effectiveness of a multifaceted tailored intervention in the implementation of three cardiovascular risk-related CPGs (hypertension, type 2 diabetes and lipids as cardiovascular risk factor) in primary care in the Basque Health Service compared with usual implementation.

### Secondary endpoints

• To evaluate the impact of the intervention on the degree of compliance with process quality indicators and subrogate clinical endpoints for the care of patients with type 2 diabetes.

• To evaluate the impact of the intervention on the degree of compliance with process quality indicators and subrogate clinical endpoints for the care of patients with hypertension.

• To evaluate the impact of the intervention on the degree of compliance with coronary risk screening process quality indicators.

• To evaluate the impact of the intervention on the prescription of statins in primary and secondary prevention.

## Methods/Design

### Study design and setting

This study is a cluster randomized trial conducted in two urban primary care districts in the Basque Health Service (Ekialde and Bilbao). These districts cover 36.9% of the population in the Basque Country. Primary care units (PCU) will be randomly assigned.

A cluster-type design is selected as the intervention was aimed at professionals working in a PCU and due to the risk of contamination between professionals working in the same PCU [27,28].

A repeated cross-sectional design is used for all patients who attend during the baseline period (pre-intervention, or “PRE”) and in the post-intervention period (“POST”), with different samples. Such an approach is appropriate when the aim of the study is to determine the impact of CPG implementation on the population and provides greater long-term power [27,28]. It also allows minor baseline differences that may arise due to cluster randomization to be compensated. The study design is shown in Figure 1.

**Figure 1 F1:**
[figure not shown]
Study design.

### Study population

Consent to participate was received from the heads of all PCUs from both districts, therefore they were all randomized (43 PCUs). All professionals (physicians and nurses) appointed to medical jobs in family medicine who agreed to participate in the study were included. Data from all patients who attend their PCU during the study period (PRE and POST intervention) and assigned to the PCUs and physicians/nurses who participate in the study will be analyzed, if they complied with one of the following inclusion criteria:

– A diagnosis of type 2 diabetes in the medical record.

– A diagnosis of hypertension in the medical record.

– Population susceptible to cardiovascular risk screening: women aged 45–74 years and men aged 40–74 years with no ischemic heart disease.

– Patients who commenced statin treatment during the study period.

– Patients diagnosed with ischemic heart disease during the study period.

The exclusion criteria are: patients assigned physicians or nurses who declined to participate in the study, younger than 14 years of age, patients assigned to physicians occupying two or more medical posts belonging to the intervention and control groups at the same time, and patients who don’t attend their PCU during the study period.

### Interventions

The control group will receive usual implementation, namely mailing of the guideline, publication in the intranet and presentation sessions in the PCU. These sessions will be led by physicians trained by the trainers responsible for teaching the intervention group.

In addition to the control group interventions, the multifaceted implementation for the experimental group also includes:

– Identical presentation sessions to those for the control group but given by physicians who took part in the guideline development process.

– The design of a specific web page with the guideline recommendations aimed at the action, with quick access, application tools (algorithms and tables with links to the main recommendations, patient materials), the possibility to ask questions, links to drug-related information.

– Three-hour workshops for family physicians and nurses, eight cardiovascular risk workshops for family physicians and a further eight for nursing staff, and four diabetic foot workshops for nursing staff. These workshops will be mostly led by the physicians responsible for the guidelines with the colaboration of two non-involved nurses.

### Endpoints

#### **
*Primary endpoints*
**

– Diabetes: percentage of patients with annual request for glycosylated haemoglobin (HbA1c).

– Hypertension: percentage of patients with annual request for basic analysis, including albumin-creatinine ratio.

– Dyslipidemia: males between 40–74 and females between 45–74 years with at least one cardiovascular risk assessment (except males and females with cardiovascular disease).

#### **
*Secondary endpoints*
**

– Diabetes: percentage of patients with HbA1c lower than 7%, percentage of patients with blood pressure lower than 140/80 mm Hg, percentage of patients with confirmed basic analysis, percentage of patients with confirmed cardiovascular risk assessment, percentage of patients with confirmed foot examination and new pharmacological treatment started with metformin.

– Hypertension: percentage of non-diabetic patients with blood pressure lower than 140/90 mm Hg, percentage of patients with annual cardiovascular risk assessment, percentage of patients starting pharmacological treatment with diuretics, beta-blockers or angiotensin-II receptor blockers.

– Dyslipidemia: percentage of patients aged between 35 and 74 years with no cardiovascular disease starting a statin treatment with previous cardiovascular risk assessment, new statin treatments in women aged over 35 years with no cardiovascular disease or diabetes, percentage of patients with a new diagnosis of coronary heart disease receiving statin treatment.

### Sample size

The following aspects were taken into account when calculating the sample size:

• On average, 45-50% of diabetic patients assigned to a healthcare professional undergo at least two annual HbA1c analyses (standard deviation 15-20%). An annual analysis is requested in around 35% of hypertensive patients. (Data taken from the Provider Agreement, 2007).

• From a clinical and operational viewpoint, an intervention strategy would be worthwhile if these averages could be increased to 55-60% for diabetes and 43% for hypertension.

• The size of the PCUs is similar, with around 10 physicians per PCU, and the number of patients assigned to each clinician is also similar.

• The intracluster correlation coefficient (ICC) is 0.10 [29-31].

In light of these considerations, approximately 100 physicians per group (10 PCUs in each group) would be needed for an α of 0.05 and a β of 0.20. Applying the cluster-related design effect gives a final number of 20 PCUs per group (intervention and control).

### Randomization

Allocation is performed by clusters. PCUs are assigned to the intervention or control group following a computer-generated randomization sequence. Randomization is performed centrally by a researcher not involved in the study who was blind to the identity of the PCU.

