### Analysis

Data will be extracted from centralized computerized medical records. Analysis will be performed at the PCU level taking the cluster design into account [32]. Indicators will be obtained for each PCU before and after the intervention and the differences will be weighted by cluster size. All analyses will be performed using Student’s *t*-test as implemented in SPSS 19. A secondary multi-level analysis will be performed using MLwiN (version 2.21) to determine the intracluster correlation coefficients (ICCs).

Analysis will be performed on an intention-to-treat basis.

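### The stated PCU-level t-test has no term for the two districts, so any change specific to one district costs precision that a one-degree-of-freedom adjustment would recover

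*Protocol article*

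**What the plan says.** All references are to the protocol article, Methods/Design.

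- **Study design and setting:** the trial takes place in "two urban primary care districts in the Basque Health Service (Ekialde and Bilbao"). The same section says that the before-after design can offset small baseline differences between arms.
- **Study population:** the heads of all PCUs consented, "therefore they were all randomized (43 PCUs"). The past tense indicates that allocation had been done.
- **Randomization:** "PCUs are assigned to the intervention or control group following a computer-generated randomization sequence". The text does not say whether the sequence was stratified or blocked by district.
- **Analysis:** "Indicators will be obtained for each PCU before and after the intervention and the differences will be weighted by cluster size". The test is then fixed: "All analyses will be performed using Student’s *t*-test as implemented in SPSS 19".
- **Analysis, secondary model:** "A secondary multi-level analysis will be performed using MLwiN (version 2.21) to determine the intracluster correlation coefficients (ICCs". Its stated purpose is to obtain ICCs; no adjustment for district is mentioned.

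**The concern.** A two-group t-test on PCU differences compares the arms and nothing else. District is a known attribute of every PCU and was fixed before allocation, yet the stated comparison does not use it.

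The before-after difference cancels a constant gap between Ekialde and Bilbao. It does not cancel a gap that opens or closes between the two periods. The primary endpoints are requests for laboratory tests and recorded risk assessments, measured over a two-year trial. Process measures of this kind could move with local ordering or management practice. The article reports no such event, so this is a risk and not an observed problem.

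Two things are at stake. First, a district-specific change inflates the between-PCU variance of the differences and lowers power, and the plan has little slack: 43 PCUs against a requirement of 40. Second, if chance gives the arms different district mixes, part of that change enters the estimate actually obtained, and the stated test cannot separate it out.

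**Working it through.** **1. The plan's own figure.** Inputs from Sample size: hypertension 35% to 43% (8 points), SD 20 points (upper end of 15-20%), α 0.05 (taken as two-sided), power 0.80, ICC 0.10, about 10 physicians per PCU.

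- The two-means formula gives 99 physicians per group (stated: about 100).
- Design effect: 1 + (10 − 1) × 0.10 = 1.9.
- 99 × 1.9 = 188 physicians, or 18.8 PCUs per group; from 100 physicians, 19 PCUs (stated: 20).

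The plan's figure is reproduced to within about one PCU.

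**2. Assumed SD of the PCU difference.** The article gives none. The SD of a PCU mean implied by its inputs is 20 × √(1.9/10) = 8.7 points, used here as a stand-in for the SD of change. The two are equal if the before and after PCU values correlate at 0.5, because the SD of a difference is 8.7 × √(2(1 − ρ)). A higher correlation makes the SD smaller and a given district change relatively more important.

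**3. Chance imbalance in district mix.** Assume arms of 21 and 22 and allocation not restricted by district. The hypergeometric probability that the arms differ by at least 20 percentage points in district share depends on the unstated PCU split:

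| PCUs in the two districts | Probability |
|---|---|
| 10 / 33 | 7% |
| 15 / 28 | 20% |
| 18 / 25 | 22% |
| 21 / 22 | 23% |

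**4. Shift in the estimate.** If one district changes by D points more than the other, an imbalance of 0.20 shifts the estimate by 0.20 × D: 1 point for D = 5 and 2 points for D = 10, against a target of 8. The standard error with no district change is 8.7 × √(1/21 + 1/22) = 2.66 points.

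**5. Added variance and power.** For a near-even split the unadjusted variance of the PCU differences is about 8.7² + 0.256 × D², where 0.256 = (21 × 22/43²) × 43/42. Power is for a true effect of 8 points, two-sided 0.05. The adjusted column is a simulation of arm plus district under unrestricted allocation.

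| District change D (points) | Unadjusted variance | Unadjusted SE | Unadjusted power | Power with district term |
|---|---|---|---|---|
| 0 | 76.0 | 2.66 | 0.84 | 0.83 |
| 5 | 82.4 | 2.77 | 0.80 | 0.83 |
| 10 | 101.6 | 3.08 | 0.72 | 0.83 |

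Simulating the unadjusted test gives the same unadjusted powers to within 0.01. If allocation had been stratified as well, adjusted power would be 0.83-0.84.

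**6. Type I error.** Over all allocations the unadjusted test rejects in 4.7-5.4% of null simulations, so it holds its level. Among allocations with an imbalance of at least 20 points (splits 15/28 and 21/22), it rejects in about 6-7% for D = 5 and 10-11% for D = 10. The adjusted test stays at about 5% in those allocations too.

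The simulations used equal cluster sizes and no weights, whereas the protocol weights by cluster size.

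**The case against.** The strongest reply is that an unadjusted cluster-level t-test is a valid analysis of a cluster randomised trial. Randomisation makes a district-specific change noise, and the t-test's standard error already reflects it. Step 6 bears this out: overall type I error stays near 5%, and the higher rates appear only after conditioning on an unlucky allocation. The before-after difference already handles stable district differences, and no district-by-time change is reported. The size rests on assumed values; at 5 points or less the gain is a few hundredths of power, and with no change adjustment loses about 0.01. All of this stands. It limits the point to precision, plus protection against an unlucky allocation.

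A reader might go further in four ways that the article does not support.

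- **That the randomisation ignored district.** The article is silent on stratification, and a condensed article commonly leaves that detail to the full protocol. If the sequence was stratified, the plain t-test would give intervals that are too wide, which is conservative.
- **That the districts are run separately.** The article names two districts of one health service with centralised records and describes no separate management.
- **That a district change biases the result.** It does not do so on average.
- **That an arm is likely to fall below 20 PCUs.** The probability of 0.54 holds only for coin-flip allocation, which is not stated, and it would matter little. A 19/24 split has the precision of 2 × 19 × 24/43 = 21.2 PCUs per arm, and 16/27 that of 20.1.

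**Conclusion.** The point holds as a low-cost improvement to the stated analysis. It is not an error in the randomisation and not a source of systematic bias. The Analysis section positively fixes a comparison with no district term in a trial drawn from two districts, and the secondary multilevel model is described only as a way to obtain ICCs.

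The benefit depends on how differently the districts change. Relative to the unadjusted test, power for the 8-point target is about 0.01 lower at no district change, 0.02-0.03 higher at 5 points and about 0.11 higher at 10 points. These figures assume an SD of change of 8.7 points, a near-even PCU split, arms of 21 and 22, and equal cluster sizes. A more uneven split lowers both the chance of imbalance and the gain. The documents give none of these quantities, so the true size cannot be fixed.

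**What to change.** In Analysis, for the three primary endpoints, replace the t-test with a linear model at PCU level: the before-after difference regressed on arm and district, weighted by cluster size as already planned. Specify this before outcome data are seen. State in Randomization whether allocation was stratified by district; if it was, the same model analyses by the stratum.

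The cost is one residual degree of freedom of about 41 (43 PCUs minus two arm means), and about 0.01 of power if the districts do not change differently. No new data are needed, since the district of each PCU is known. No change to the allocation is requested, because the article says that the PCUs had already been randomised.
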